### Sample Size Determination

On the basis of previous studies, psychosocial and educational interventions in the perinatal period generally produce a medium size effect on outcome variables [27,28]. Hence, the SEPP intervention can also be assumed to have a medium effect size on outcome variables. A repeated measure analysis of covariance (ANCOVA) will be used to test for differences between two groups (intervention and control) and within four separate time points and for interaction (group x time) effects. The required sample size for the detection of a medium effect size of 0.3 (analysis of variance [ANOVA] *F* value) at a power of 80% and a significance level of 5% (two-sided) is 45 in each group [40]. Considering a 30.0% (30/100) attrition rate based on previous studies [27,29], a minimum of 118 participants (45x2 + 45x2x30%=90 + 28=118), with 59 in each group, is needed. A purposive sample of approximately 16 participants will be needed for the process evaluation. Parents with differing mean parenting efficacy (primary outcome) scores from both the intervention and control groups (8 from each group) will be selected to participate in the face-to-face interviews, until data saturation is attained.

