**Methods:**

A randomized controlled two-group pretest and repeated posttest experimental design will be used. The study will recruit 118 parents (59 couples) from the antenatal clinics of a tertiary public hospital in Singapore. Eligible parents will be randomly allocated to receive either the supportive educational parenting program or routine perinatal care from the hospital. Outcome measures include parenting self-efficacy, parental bonding, postnatal depression, social support, parenting satisfaction, and cost evaluation. Data will be collected at the antenatal period, immediate postnatal period, and at 1 month and 3 months post childbirth.

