## Methods

### Design

A randomized controlled two-group pretest and repeated posttest experimental design will be used. Couples (n=118 participants) recruited from a tertiary hospital will be randomly assigned into the two groups (intervention group receiving the SEPP and routine care or control group receiving only routine care). Data will be collected via questionnaire surveys using locally validated and reliable instruments, medical reviews, semistructured face-to-face interviews, and telephone interviews.

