### Participants

The participants recruited will be couples (a father and mother dyad is considered one couple). The inclusion and exclusion criteria for participants who are mothers are shown in Textboxes 1 and 2.

The inclusion criteria for fathers are those who (1) are 21 years and above, (2) are able to read and speak English, (3) have a mobile phone with Internet access, and (4) plan to stay in Singapore for the first 3 months post delivery. The exclusion criteria for fathers are those who have self-reported physical or mental disorders that will interfere with their ability to participate in the study and/or are a single parent.

All couples are recruited antenatally and will be told beforehand that they may be excluded from the study if mothers are to experience complication during their pregnancy and the delivery of their newborn.

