### Data Analysis

All quantitative data will be analyzed using Statistical Package for the Social Sciences (SPSS) version 24.0 (IBM Corp). Missing data will be replaced (assuming 10%) for intention-to-treat (ITT) analysis. Both ITT analysis and per-protocol analysis will be conducted to compare any differences between groups. Descriptive statistics such as mean, standard deviation, and range for continuous dates, frequencies, and percentages will be used for nominal and ordinal data. Cronbach alpha will be used to test the internal consistencies of the questionnaires. Inferential statistics such as the independent *t* test or ANOVA will be used to compare differences of outcomes between or among demographic subgroups. Presuming that outcomes variables are normally distributed, parametric tests will be used. Repeated measures ANCOVA adjusted for confounding variables will be used to test the effect of intervention on outcome variables across four time points. Univariate ANCOVA will be used to test the differences in outcome variables between two groups at the interim and two posttests data separately.

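### The sample size and the named analyses have no couple level, so pooling both parents would overstate precision, and the stated 80% power assumes that partners are uncorrelated

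*Protocol article*

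**What the plan says.** The unit of recruitment is the pair. In the Participants section "a father and mother dyad is considered one couple". The Abstract counts both members towards the total: "The study will recruit 118 parents (59 couples) from the antenatal clinics of a tertiary public hospital in Singapore". The Design section allocates pairs and counts people: "Couples (n=118 participants) recruited from a tertiary hospital will be randomly assigned into the two groups". The Results section reports enrolment so far as 49 couples, 27 in the intervention arm and 22 in control, so partners appear to share an arm.

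The Sample Size Determination section starts from "The required sample size for the detection of a medium effect size of 0.3" and states that the number required "at a power of 80% and a significance level of 5% (two-sided) is 45 in each group". After an attrition allowance it arrives at "a minimum of 118 participants (45x2 + 45x2x30%=90 + 28=118), with 59 in each group, is needed". It mentions no pairing and no within-couple correlation.

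For the analysis, the Data Analysis section says "Repeated measures ANCOVA adjusted for confounding variables will be used to test the effect of intervention on outcome variables across four time points", followed by univariate ANCOVA at each later time point. Neither model is given a couple term, and nothing there says that mothers and fathers are analysed separately.

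Two passages sit awkwardly with the rest. The Results section gives the recruitment target as 118 couples, not 59. The Randomization section prepares 118 numbers and has participants draw one, without saying whether a couple draws once or each parent draws.

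**The concern.** Two parents of the same newborn, in the same arm, answer the same scales about the same baby. One scale asks about support from the partner. The article's own theoretical framework treats self-efficacy, bonding, mood and social support as interrelated. Zero correlation between partners is therefore a strong assumption, yet both the sample size and the named models make it.

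A repeated measures ANCOVA handles the correlation of one parent's scores over time. It does not handle the correlation between two parents. If both are entered as separate subjects, the treatment comparison is credited with more independent information than it has. P values and confidence intervals for the primary outcome (parenting self-efficacy) and the other parent-level outcomes would then be too favourable, in the direction of false positives. The power statement would also rest on more independent units than exist.

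**Working it through.** **Inputs from the protocol article.** Effect size 0.3, 80% power, 5% two-sided, 45 per group (Sample Size Determination); two parents per couple (Participants); 118 parents as 59 couples (Abstract). The 0.3 is read as Cohen's f, so for two equal groups d = 2f = 0.6 SD.

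**Assumed.** Within-couple correlation ρ of the analysed outcome: 0.1, 0.3, 0.5. The document gives none.

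**1. Reproduce the stated figure.** For a two-group F test on independent people measured once, the noncentrality is N·f² with N the total.
- 44 per group: N·f² = 88 × 0.09 = 7.92, power 79.5%.
- 45 per group: N·f² = 90 × 0.09 = 8.10, power 80.4%.

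So 45 is the first size to reach 80%. Four-measure variants tried with f = 0.3 do not give 45: the between-group effect needs 22 to 42 per group for within-person correlations of 0.3 to 0.9, and the group-by-time interaction 12 or fewer.

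**2. Design effect.** With both partners in one arm, the variance of the group difference is multiplied by 1 + (2 − 1)ρ = 1 + ρ.

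**3. Type I error of a test that ignores the couple**, 2[1 − Φ(1.96/√(1 + ρ))]:
- ρ = 0.1: 1.96/√1.1 = 1.869, giving 6.2%.
- ρ = 0.3: 1.96/√1.3 = 1.719, giving 8.6%.
- ρ = 0.5: 1.96/√1.5 = 1.600, giving 11.0%.

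Simulation (20,000 trials per setting, 23 against 22 couples) gave 5.8%, 8.5% and 11.2%. A test on couple means in the same simulations stayed at 4.7% to 5.0%.

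**4. Power of a valid test, single measure**, 45 parents per group, effective number 45/(1 + ρ):
- ρ = 0.1: 40.9 per group, 76.5% by the F test and 77.4% by the normal approximation, so about 77%.
- ρ = 0.3: 34.6 per group, 69%.
- ρ = 0.5: 30.0 per group, 63%.

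To keep 80% on this basis, 45(1 + ρ) parents per group must be analysed: 50, 59 or 68, that is 100, 118 or 136 in total instead of 90.

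**5. What repeated measures could recover.** Assume f = 0.3 at each of three post-baseline measures, averaged per parent, with within-person correlation w (also not given). The effective number is multiplied by 3/(1 + 2w).
- w = 0.5, factor 1.5: effective 61.4 / 51.9 / 45.0 per group, power about 91% / 85–86% / 80%.
- w = 0.7, factor 1.25: effective 51.1 / 43.3 / 37.5 per group, power about 85% / 79% / 72–73%.

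**6. If the target were 118 couples.** That is 118 parents per arm, about 82 after 30% loss. Dividing by 1 + ρ gives 74.5 / 63.1 / 54.7, and single-measure power of 95% / 92% / 87%.

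**The case against.** The strongest objection concerns power. A reader might infer that the trial cannot reach 80%. The document does not support that. The single-measure calculation is not the planned repeated measures analysis, and step 5 shows that averaging over time could restore some or all of the loss, depending on two correlations that are not stated. The Results section's target of 118 couples would remove the shortfall altogether. This objection stands, and the power point must be conditional. It does not rescue the stated calculation, which takes 45 from an independence formula without claiming any gain from repeated measures.

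Second, pooling is inferred. The article does not say that both parents enter one model, and a fuller protocol or analysis plan, not shown, might add a couple term or analyse mothers and fathers separately. That would cure the error rate. It would not cure the sample size if the target is 59 couples, because separate analyses leave about 30 per arm for each parent.

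Third, the Randomization wording could be read as each parent drawing a number. If partners were split across arms, a test ignoring the couple would be conservative: simulated type I error 3.8% / 2.1% / 0.6% at ρ of 0.1 / 0.3 / 0.5. The Design section and the enrolment counts by couple make the shared-arm reading the more likely one, but the text should say so. Independence fails either way.

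**Conclusion.** The point holds, conditionally. The sample size is counted in individuals as if independent, and the named analyses have no couple level, in a trial whose unit is the couple. If parents are pooled as written and partners share an arm, any positive within-couple correlation makes the main test anti-conservative: about 6.2% / 8.6% / 11% instead of 5% at assumed correlations of 0.1 / 0.3 / 0.5. The inflation does not depend on whether the target is 59 or 118 couples.

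The power loss, to about 77% / 69% / 63%, applies to the protocol's own single-measure basis with 45 parents per group. It should not be read as the power of the final analysis. The attrition step in the sample size section is a separate matter and is left out of these figures.

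**What to change.** - **Analysis.** Account for the couple. One way is a linear mixed model with a couple random effect, repeated measures within parent, and parent role (mother or father) as a fixed effect. Couple-robust standard errors would serve as well.
- **Target and allocation.** Reconcile the Abstract, Design, Sample Size Determination, Randomization and Results sections on whether the target is 59 or 118 couples, and state that each couple draws one allocation.
- **Power.** Restate it in the Sample Size Determination section in couples, over a stated range of within-couple correlation. If credit is taken for repeated measures, give the within-person correlation assumed.

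The cost is a less favourable stated power and slightly more analysis work. The analysis change needs no additional data. If the restated power is too low for the chosen number of couples, the sponsor must either accept that openly or revisit the target.

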### Randomization

The research randomizer will be used to randomly generate one set of 59 numbers ranging from 1 to 118. Generated numbers are assigned to the intervention group and the remaining to the control group. All 118 numbers will be placed in an opaque envelope. The principle investigator who will not be involved in the recruitment will hold the random numbers and pass it to RA1 for recruitment. After assessing eligibility and obtaining informed consent, the participants will be asked to pick a number from the opaque envelope, in which the number picked will determine the groups assigned.

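### The 30% attrition allowance is added to the completers instead of divided out, so 118 participants retain about 41 per group at that attrition, not the required 45

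*Protocol article*

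**What the plan says.** The Sample Size Determination section of the protocol article assumes a standardised effect of 0.3 on the ANOVA scale. It gives the number needed "at a power of 80% and a significance level of 5% (two-sided) is 45 in each group". It then allows for loss, "Considering a 30.0% (30/100) attrition rate based on previous studies", and concludes that "a minimum of 118 participants (45x2 + 45x2x30%=90 + 28=118), with 59 in each group, is needed".

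The Randomization section builds the allocation list on this total: the plan will "randomly generate one set of 59 numbers ranging from 1 to 118" and give those numbers to the intervention. The Abstract gives the same 118 as parents in 59 couples, and the Design section counts 118 participants.

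**The concern.** A 30% attrition rate is a fraction of the people who enter the trial. The article applies it to the people who must finish and adds the result. That always gives too small a recruitment target, and the gap widens as the assumed attrition rises. Here the figure described as a minimum does not leave the section's own 45 per group once its own attrition rate is applied.

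At stake is whether the published total supports the 80% power claim. The randomization list is fixed at this total. The Results section says that recruitment was still under way, so the statement could still be corrected.

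**Working it through.** **Inputs, all from Sample Size Determination:** effect f = 0.3; two-sided alpha 5%; power 80%; 45 completers per group (90 in total); attrition 30%; recruited total 118 (59 per group). The equal split is confirmed in Randomization. The 118 is read as individuals, as in the Abstract, Design and Sample Size Determination.

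**1. Reproduce the 45.** For two groups d = 2f = 2 x 0.3 = 0.6. A two-sample comparison at one time point (noncentral t, two-sided 5%, 80% power) needs 44.6 per group, which rounds up to 45. Power at 45 per group is 80.4%. The article's figure is therefore that of a simple two-group comparison.

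**2. Reproduce the 118.** The additive rule gives 90 x (1 + 0.30) = 117, or 58.5 per group. Rounding each group up gives 59, and 2 x 59 = 118. The printed sum reaches 118 by writing 28 for 90 x 30%, which is 27.

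**3. Apply the stated attrition to the stated total.** 118 x (1 - 0.30) = 82.6, or 41.3 per group. That is 7.4 fewer completers than the 90 required.

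**4. Correct inflation.** 90 / (1 - 0.30) = 128.6, so 129. With equal arms this becomes 130, or 65 per group, of whom 65 x 0.70 = 45.5 remain. The recruitment target is short by 129 - 118 = 11, or by 130 - 118 = 12 with equal arms.

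**5. Attrition that 118 can absorb.** 1 - 90/118 = 23.7%.

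**6. Power at 30% attrition, on the basis of step 1 (d = 0.6):**

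| Completers per group | Noncentral t | Normal approximation |
|---|---|---|
| 45 | 80.4% | 81.2% |
| 41.3 | 76.9% | 77.8% |
| 41 | 76.5% | 77.5% |

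By the noncentral t, the loss from 45 to 41.3 per group is 80.4 - 76.9 = 3.5 points.

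**7. Sensitivity to the planned model.** The article plans a repeated-measures ANCOVA over four time points and states no correlation between measurements. For the between-group F test averaged over four measurements, with f = 0.3, 82 completers and partners treated as independent, the noncentrality is 82 x 0.09 x 4 / (1 + 3 x rho). The values of rho below are assumptions:

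| Assumed rho | Power at 82 completers |
|---|---|
| 0.5 | 92.4% |
| 0.7 | 86.2% |
| 1.0 | 76.5% |

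At rho = 1 the extra time points add nothing, and the result equals the single-time-point figure for 41 per group.

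**The case against.** The strongest objection is that 77% is not the power of the planned analysis. It belongs to an unadjusted comparison at one time point. As step 7 shows, a between-group test over four measurements could exceed 80% with 82 completers at plausible correlations. This stands. A reader might infer that the trial's planned analysis falls below 80% power, and the article does not support that inference. It does not support the opposite assurance either: no correlation is stated, the 45 per group takes no credit for repeated measures, and the step 7 figures ignore correlation between partners and do not cover the group-by-time test.

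Second, the loss is conditional. It arises in full only if attrition reaches 30%, and up to 23.7% the required 90 remain. This also stands, but 30% is the article's own planning figure.

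Third, a reader might take the 28 as a cause of the shortfall. It is not. It most plausibly reflects rounding up to equal arms, and it raises the total by one, which slightly reduces the gap.

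Fourth, a reader might take the word medium to imply a smaller effect than 0.3 and hence a larger deficit. The article fixes the effect numerically at 0.3, and that value reproduces 45, so there is no ground for substituting another.

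Fifth, the Data Analysis section plans to replace missing values, assuming 10%. Replacement does not restore the information lost with participants who leave, and 10% does not match the 30% used for the sample size.

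Finally, the Results section speaks of 118 couples. That contradicts the Abstract's 59 couples and is a separate matter. The head-count here rests on the reading used where the sample size is derived.

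**Conclusion.** The inflation step is wrong as printed, and nothing else in the article repairs it. At the article's own 30% attrition, 118 individuals leave about 82 to 83 completers, or 41 per group, against the required 45. The target is 11 participants short of 129, or 12 short of 130 with equal arms. On the comparison that reproduces 45 per group, power is about 77% rather than 80%.

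This rests on three conditions: 118 counts individuals, attrition reaches the full 30%, and power is judged on the single-time-point, two-group basis with no allowance for correlation within couples. The error is clear but modest. It concerns the stated justification of the sample size; it does not bias any estimate and does not show that the planned repeated-measures analysis is underpowered.

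**What to change.** In Sample Size Determination, replace the additive sum with 90/0.70 = 129 (130 with equal arms). This also removes the 27/28 slip. If the trial keeps 118 participants, add one of two statements:

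- Power is about 77% if attrition reaches 30%, for the two-group, single-time-point comparison with f = 0.3 and before any allowance for within-couple correlation.
- The 80% on that same basis holds only up to about 23% attrition.

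The cost is one corrected line and a slightly less favourable stated power or attrition limit. Neither statement requires extra enrolment or a change to the analysis.

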### Randomization

The research randomizer will be used to randomly generate one set of 59 numbers ranging from 1 to 118. Generated numbers are assigned to the intervention group and the remaining to the control group. All 118 numbers will be placed in an opaque envelope. The principle investigator who will not be involved in the recruitment will hold the random numbers and pass it to RA1 for recruitment. After assessing eligibility and obtaining informed consent, the participants will be asked to pick a number from the opaque envelope, in which the number picked will determine the groups assigned.

### Outcome Measures and Instruments

Patients’ demographic data (eg, age, gender, ethnicity, and education) will be collected. In addition, the following instruments will be used to measure parental outcomes:

Parenting Efficacy Scale (PES): This 10-item PES scale [41] is used to measure parental beliefs on self-efficacy. Nine of the items refer to specific behaviors related to infant care (eg, feeding and bathing), and the last item is a global evaluation of parenting ability. The total score of PES ranges from 10 to 40, with higher scores indicating higher PSE. The Cronbach alpha value of the PES was .74 in the previous study [42].Parent- Infant Bonding Questionnaire (PIBQ): This is an 8-item, 4-point Likert scale used to measure the parental bonding of both parents [43]. The total scores range from 0 to 24, with higher scores suggesting ineffective bonding between mother and infant and vice versa. The cut-off score indicating poor bonding between parent and infant is indicated at 2 [44]. The Cronbach alpha for this questionnaire was .7 in the previous study [45].Edinburgh Postnatal Depression Scale (EPDS): This is a 10-item scale widely used to measure parents’ postnatal depression [24,29,46-48]. The total score of the EPDS ranges from 0 to 30. The recommended cut-off score of 12 or 13 is used for screening probable cases of postnatal depression. The sensitivity of the EPDS ranges from 68% to 80%, with 77% specificity and a Cronbach alpha of .88 [49].State Trait Anxiety Inventory (STAI): This is a 40-item 4-point Likert scale used to measure parental anxiety level. The total score for the STAI ranges from 40 to 160, with higher scores indicating greater levels of parental anxiety. The scale has been tested widely in various studies [50-53]. The Cronbach alpha for the STAI was .8 in a previous local study [52].Perceived Social Support for Parenting (PSSP): This is a 4-item scale [42] used to measure the social support parents receive from their partners or others. The score of the 5-point Likert scale ranges from 0 to 20 for the support received from partners or others. The instrument showed high internal consistency and had a Cronbach alpha of .81 in a previous study [42].What Being the Parent of a Baby is Like (WBPL): The evaluation subscale of the WBPL will be used to measure parenting satisfaction [54]. It consists of 11 items, and each item is a 10-point semantic differential scale ranging from 0 (none of the phenomenon) to 9 (a great deal of the phenomenon). In previous studies, the Cronbach Alpha ranged from .91 to .92 [54,55].Health care utilization and program-related expenses sheet: This sheet will be used to capture all direct health systems cost related to health care services utilized antenatally and postnatally because of maternal or infant related health issues such as hospital admissions and outpatient contacts, health professional’s time, program-related time, and during pregnancy, for the first and 3rd month after delivery. The study will take an *all-payer* health system perspective in which it will attempt to capture all resources that are used by the participants, regardless of who the payer is (ie, government or consumer), including the program cost. The measurement period begins from entry into the program until 3 months post birth.A semistructured interview guide will be used for the process evaluation. Individual face-to-face interviews will be conducted immediately after the intervention (1 month post birth) to identify strengths and weaknesses and to comment on the content, activities, effectiveness, and delivery methods of the SEPP for participants in the intervention. Parents in the control group will be asked to comment on the current routine perinatal care provided by the hospital. All interviews will be audiorecorded.

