### Aims

The aims of the study were to (1) examine the effectiveness of the SEPP on parental outcomes, including PSE (primary outcome), parental bonding, postnatal depression and anxiety, social support, and parenting satisfaction; (2) evaluate the cost-effectiveness of the SEPP compared with routine perinatal care; and (3) process evaluation of the SEPP by assessing its strengths and weaknesses from parents’ perspectives.

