### Hypotheses

The hypotheses are (1) When compared with those in the control group receiving routine care, parents receiving the SEPP will report significantly (a) higher levels of self-efficacy in newborn care, (b) higher levels of parental bonding, (c) lower levels of depression and anxiety, (d) higher levels of social support received, and (e) higher levels of parenting satisfaction and (2) It is more cost-effective to provide the SEPP than routine care.

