3	mHealth^b^ app-based follow-up educational session	1 month access to the mHealth app	A knowledge-based content on topics including newborn and maternal care Audio recordings of the knowledge-based content Videos on various newborn care tasks such as baby bathing and breastfeeding demonstrated by a trained midwife using a live baby. Each video is approximately 8 min long on average A discussion forum Push notifications

^a^Number in series.

^b^mHealth: mobile health.

The knowledge-based content in the mHealth app includes evidence-based information on ways to enhance parental self-efficacy and bonding, newborn care and maternal self-care tasks, emotional challenges and ways of dealing with it, breastfeeding-related information, and insights for new parents for a smooth transition to parenthood. The discussion forum will be a platform for parents to ask any questions they might have. All parental queries will be answered by a trained midwife (research assistant 1, RA1) once a day for the first 4 weeks post childbirth because this period is the most stressful period for new parents in the early post-partum period [38,39]. Additionally, other parents can also provide insights to these queries by sharing their personal experiences. According to Bandura’s self-efficacy theory [33], self-efficacy and a help-seeking behavior (social support) can be enhanced when tasks are learned from others in a similar situation; therefore, parents are encouraged to interact with other parents in the discussion forums. Daily push notifications regarding important milestones on parenting will be sent to users. Each notification appears on the user’s home screen, which aims to pique the user’s interest and serves as a reminder to continue exploring the rest of the content-rich app. Participants’ access to the mHealth app will be monitored (by adding the function of time spent in accessing materials) to record the dosage of the intervention each participants receives. The app was developed by an external vendor who is an expert in mHealth app development. The research team and the external app developer have been keeping in close contact for the development of the app. Screenshots of the features of the app as examples are shown in Figures 2-6.

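### Hypothesis 1(c) on anxiety, a non-primary outcome, rests on one combined State Trait total; naming the state score would fit the question better and avoid a dilution of assumption-dependent size

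*Protocol article*

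**What the plan says.** The Aims list the outcomes as "including PSE (primary outcome), parental bonding, postnatal depression and anxiety, social support, and parenting satisfaction", so anxiety is one of the non-primary outcomes. Hypothesis 1(c) predicts "lower levels of depression and anxiety" in the SEPP group.

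Under Outcome Measures and Instruments, the State Trait Anxiety Inventory is the only anxiety measure: "This is a 40-item 4-point Likert scale used to measure parental anxiety level". Its scoring is then given as one figure: "The total score for the STAI ranges from 40 to 160, with higher scores indicating greater levels of parental anxiety". No state or trait score is mentioned. The same section does name a subscale where one is meant: for parenting satisfaction it specifies the evaluation subscale of the WBPL.

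Table 1 describes the program as a 30-minute antenatal telephone session, a 60-minute postnatal session and "1 month access to the mHealth app". Data Collection sets four measurement points, from pregnancy to 3 months after birth. Data Analysis plans a repeated measures ANCOVA that "will be used to test the effect of intervention on outcome variables across four time points", plus separate ANCOVAs at the interim and the two posttest points.

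**The concern.** The question in 1(c) is whether the program makes parents less anxious over the weeks around and after birth. The reasons given for the time points concern changing circumstances: the challenges of the first month, and the return to work at about 3 months. That is a question about current anxiety. By its name, the inventory also measures a disposition, and a single total adds the two together.

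If the dispositional part responds less than the current part, it adds variance to the score with little signal. A real fall in current anxiety is then harder to detect, and the total does not show which component a difference came from. One of the stated hypotheses depends on this score.

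**Working it through.** **Inputs from the article.** 40 items on a 4-point scale, total 40 to 160 (Outcome Measures and Instruments). Effect size f = 0.3 for outcome variables in general, power 80%, two-sided 5%, 45 per group (Sample Size Determination).

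**Assumptions, not in the article.** Items scored 1 to 4. Two 20-item halves with equal SDs (set to 1). The effect falls on the state half only, except where stated. Correlations as listed below.

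**1. The plan's own figures.**
- Range: 40 × 1 = 40 and 40 × 4 = 160, so the stated range is that of all 40 items. A 20-item subscale would run from 20 to 80.
- Sample size: for two groups d = 2f = 0.6. The normal approximation gives 44 per group. The exact t test gives 79.5% power at 44 and 80.4% at 45. The stated 45 is reproduced.

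**2. One posttest, no baseline adjustment.** With state-trait correlation ρ, the SD of the sum is √(2(1+ρ)), so d(total) = 0.6/√(2(1+ρ)).

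| ρ | d on total | Power at 45 per group |
|---|---|---|
| 0 | 0.42 | 51% |
| 0.5 | 0.6/√3 = 0.35 | 37% |
| 0.8 | 0.6/√3.6 = 0.32 | 32% |
| 1 | 0.6/√4 = 0.30 | 29% |

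The state score alone has 80%. If trait moves one third as much as state, the numerator becomes 0.6 × 4/3 = 0.8. For ρ = 0.5 to 0.8, d is then 0.46 to 0.42 and power 58% to 51%.

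**3. Adjusted for the baseline value of the same score.** Let a be the state retest correlation, b the trait retest correlation and c the state-trait correlation (taken as equal within and across times). For state, d = 0.6/√(1−a²). For the total, the variance is V = 2+2c, the baseline-to-posttest covariance is C = a+b+2c, and d = 0.6/√(V − C²/V).

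Worked case, a = 0.5, b = 0.85, c = 0.5: V = 3, C = 2.35, residual variance 3 − 5.5225/3 = 1.159, so d(total) = 0.6/1.077 = 0.557 and power is 74%. For state, d = 0.6/√0.75 = 0.693 and power is 90%.

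Over b = 0.75 to 0.95 and c = 0.5 to 0.65:

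| a | State: d, power | Total: d, power |
|---|---|---|
| 0.4 | 0.655, 87% | 0.493 to 0.557, 64% to 74% |
| 0.5 | 0.693, 90% | 0.520 to 0.600, 69% to 80% |
| 0.6 | 0.750, 94% | 0.554 to 0.658, 74% to 87% |

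The total does worse than state in every case tried.

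**4. Change scores.** For state, d = 0.6/√(2−2a). For the total, 2V − 2C = 4 − 2a − 2b, so d = 0.6/√(4−2a−2b). If b = 1 this equals the state value, so a perfectly constant trait half cancels and nothing is lost. With b below 1 some loss returns: at a = 0.5 and b = 0.85, d is 0.526 against 0.600 and power 70% against 80%.

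**The case against.** The case against has several parts, and most of it limits the point rather than removing it.

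- **The premise is partly outside the documents.** Apart from the instrument's name, the article says nothing of state and trait. It does not give an equal split, say that trait is stable, or say that the program cannot move it. This stands, so those items are assumptions with ranges. The two-part construct is in the printed name.
- **The sentence gives a range and does not define an endpoint, and a condensed article may leave scoring to a fuller document.** This stands in part. If the full protocol or an analysis plan names the state score, only the article's wording needs aligning. As written, however, the 40-item total is the only anxiety score given, in a section that names a subscale for another instrument.
- **Placing f = 0.3 on the state half is a choice.** This stands. The article assumes a medium effect on outcome variables generally. If that refers to the total as measured, power on the total meets the plan's figure.
- **The planned analysis uses baseline.** The repeated measures ANCOVA spans four time points including baseline, so the unadjusted 32% to 37% should not be read as the power of the planned test. The separate ANCOVAs do not name baseline as a covariate, so the unadjusted case keeps some relevance there.

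A reader might infer that a difference in the total cannot be interpreted. The working does not support that: if trait is unmoved, the raw difference in the total is exactly the raw state difference, and only its size relative to the SD shrinks. A reader might also take the intervention to last only 4 weeks. That figure is the app access; the program starts with an antenatal session, and outcomes run to 3 months.

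**Conclusion.** The point holds in a limited form. The article gives hypothesis 1(c) a single combined State Trait total, and the state score would match the question better.

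The size of the loss is not fixed by the documents. With equal halves, an unmoved trait half, d = 0.6 on state and 45 per group, power is about 32% to 37% against 80% on an unadjusted posttest (ρ = 0.8 to 0.5). With baseline adjustment it is about 64% to 87% against 87% to 94%, and this is the fairer guide to the planned analysis. The loss is nil in a change-score analysis if trait is perfectly constant.

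It would be tempting to conclude that the trial is underpowered or that its main result is at risk. The documents do not support that: parenting self-efficacy is the primary outcome, and the sample size was not calculated for anxiety in particular.

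**What to change.** In Outcome Measures and Instruments, state that the STAI state subscale score at each time point is the tested anxiety outcome for hypothesis 1(c). Use the baseline trait score as a covariate or descriptor, and report the 40-item total descriptively. If the sponsor prefers to test the total, give the reason.

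Keep collecting all 40 items at every visit. The Results section reports 49 couples already enrolled, and shortening the questionnaire now would make the data differ between earlier and later participants.

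The cost is a short scoring statement and no new data. It should be settled before outcomes are compared by group, so that the choice of score cannot be influenced by the results. The downside is less direct comparison with studies that report the total, which the descriptive reporting partly covers.
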